### PCR Testing

#### DNA Extraction

DNA extraction will be carried out using the Invitrogen PureLink Genomic DNA Mini Kit (Thermo Fisher Scientific) according to the manufacturer’s instructions.

#### Real-Time PCR for RLEP

PCR targeting the repetitive element (RLEP) of *M leprae* will be used to detect the presence of this microorganism in the perineural aspirate. Reactions will be performed in a final volume of 30 μL containing 1X reaction buffer, 0.2 mM of deoxyribose nucleoside triphosphates, 1.5 mM of magnesium chloride, 1 U of Platinum Taq DNA Polymerase (Invitrogen), 0.2 μM of the primers 5′-CTTGCACCATTTCTGCCGCT-3′ and 5′-TGCGCTAGAAGGTTGCCGTA-3′ (Invitrogen), ultrapure water, and 50 to 100 ng of genomic DNA. Amplification will be performed using a QuantStudio 3 system (Thermo Fisher Scientific) with an initial denaturation period of 3 minutes at 94 °C followed by 15 cycles at 94 °C for 30 seconds, 56 °C for 30 seconds, and 72 °C for 30 seconds and 20 cycles at 94 °C for 1 minute, 56 °C for 30 seconds, and 76 °C for 1 minute.

#### RNA Extraction and Treatment With Deoxyribonuclease and cDNA Formation

RNA extraction, treatment with deoxyribonuclease, and cDNA formation will be carried out using validated kits according to availability of the dermatomycology laboratory of the University of Brasília Faculty of Medicine. High–molecular weight RNA will be purified using the mirVana PARIS Kit (Thermo Fisher Scientific) with 500 μL of perineural aspirate. RNA will be quantified spectrophotometrically (NanoDrop 2000 and 2000c; Thermo Fisher Scientific). A total of 500 ng of RNA will be converted to cDNA using the PureLink RNA Mini Kit (Thermo Fisher Scientific).

#### Real-Time PCR for sodA and 16S Ribosomal RNA

For these reactions, the primers targeting 16S ribosomal RNA (5′-GCATGTCTTGTGGTGGAAAGC-3′, 5’-CACCCCACCAACAAGCTGAT-3’, and probe 5′-CATCCTGCACCGCA-3′) and sodA (5’-ACCACGCCGCATATGTCA-3′, 5’-CGCGTGCCTCGTCAAGT-3’, and probe 5’-TGGCAAGCGCGTCATTGACACCT-3’) will be used. We will add 5 µl of purified *M leprae* cDNA to a mixture containing 25 µl with 2X TaqMan Universal PCR Master Mix (Thermo Fisher Scientific), 500 nM of each primer, and 100 nM of each probe. Reaction mixtures will be subjected to 50 °C for 2 minutes, 95 °C for 10 minutes, and 40 cycles at 95 °C for 15 seconds and 60 °C for 1 minute. Amplification will be performed using a QuantStudio 3 system (Thermo Fisher Scientific).

### PCR Positivity Criteria

A DNA or RNA sample will be considered positive if all the following criteria are met: threshold cycle (Ct) of 30 or less, standard amplification curve with exponential and plateau phases, and significant amplification of the positive controls with no amplification meeting the previous criteria for the negative controls. In the absence of a Ct of 30 or less or in the case of an amplification curve that does not meet the criteria above, the sample will be considered negative. Accuracy using this Ct value will be the main finding of the study, being compared with the conventional diagnostic tests and ultrasound examination. We will also construct receiver operating characteristic curves with different Ct values to evaluate whether setting different thresholds can improve the accuracy of the test compared to the preplanned value. If there is no amplification in the positive controls, or if there is amplification of the negative controls, real-time PCR for all samples in the plate will be repeated. Missing values will be dealt with using multiple imputation.

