**Methods:**

This will be a diagnostic study with consecutive prospective recruitment of patients referred to the leprosy outpatient clinic of University Hospital of Brasília for diagnosis and treatment. During follow-up, clinical and molecular examinations will be performed, and their results will be compared to the sonographic findings, which will be collected monthly for 1 year. Patients will be evaluated clinically, via ultrasound, and molecularly in 2 stages of leprosy diagnosis and treatment: immediately after clinical diagnosis and 1 year after the start of treatment. Subcutaneous aspiration of the ulnar nerve will be performed in the ulnar tunnel guided by ultrasound. The aspirated material will be used for identification of bacillary DNA and RNA at the time of diagnosis and 1 year after the start of treatment.

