**Conclusions:**

We believe that ultrasound-guided perineural aspirate will increase the accuracy of leprosy diagnosis and may demonstrate the viability of the bacillus before and after treatment via RNA identification.

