### Diagnostic Accuracy

The measure of diagnostic accuracy for the main objective will be the accuracy of PCR for the detection of *M leprae*. We will also calculate specificity and sensitivity of the method and of real-time PCR for the detection of *M leprae* viability. AUC will be calculated for quantitative variables obtained using ultrasound examination.

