Through our study, we will be able to demonstrate a high sensitivity of the perineural aspirate in patients with paucibacillary forms of the disease. Preliminary studies in patients that have undergone nerve biopsies have shown both a high sensitivity (92% using PCR) [45] and higher bacillary index of nerve sampling compared to skin sampling [46]. The current diagnostic strategy, which samples for the microbiological diagnosis of leprosy from skin lesions, earlobes, and 3 to 6 representative skin locations [47,48], has an especially low sensitivity in paucibacillary, pure neural, and early-stage lesions [49,50], resulting in diagnostic delays, misdiagnosis [51], and mistreatment. Our potentially higher diagnostic sensitivity in paucibacillary forms is a consequence of the traditional pattern of sample collection not matching the pattern of distribution and homing of *M leprae* in the natural history of the disease. The peripheral nervous system seems to be the first to harbor this mycobacterium [52] and is the location of persistent parasites after treatment of multi-bacillary disease [53].

In this study, we will evaluate both RLEP and RNA targets (sodA and 16S). Previous studies have evaluated a variety of PCR targets to detect *M leprae* in tissues, with the most frequently used being RLEP [13]. Despite its high specificity, the use of this target can only detect 75% of patients with leprosy [13], and its positivity is not related to the viability of the microorganism [15]. We expect to obtain high assay sensitivity using these tests in parallel, as it has been proposed in other studies [14]. As *M leprae* viability is an important clinical question in leprosy, especially in terms of differentiating reaction from relapse, we will also use RNA targets. Their use better correlates with active microorganisms as this nucleic acid is less resistant to temperature and has a shorter half-life [54], being already used for viability evaluation in preliminary studies [15,41]. Thus, our proposed test is also expected to deliver information on the viability of *M leprae* in the aspirate.

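### The single Ct 30 cut-off used to read the RNA viability marker before and after treatment cannot separate a smaller sampled bacterial load from a loss of viability

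*Protocol article*

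**What the plan says.** Under Methods, PCR Positivity Criteria, the protocol article sets one rule for DNA and RNA alike: "A DNA or RNA sample will be considered positive if all the following criteria are met: threshold cycle (Ct) of 30 or less", together with an acceptable amplification curve and valid controls. The complement is negative: "In the absence of a Ct of 30 or less or in the case of an amplification curve" that fails the criteria, the sample counts as negative. There is no intermediate category, and a plate is repeated only when its controls fail.

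The aspirate is used for "identification of bacillary DNA and RNA at the time of diagnosis and 1 year after the start of treatment" (Abstract, Methods). The RNA result is tied to viability in three places:

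- The Abstract's Conclusions say that the technique "may demonstrate the viability of the bacillus before and after treatment via RNA identification".
- The Discussion, under Expected Findings, says that "our proposed test is also expected to deliver information on the viability of" *M leprae*.
- The Diagnostic Accuracy section plans "specificity and sensitivity of the method and of real-time PCR for the detection of" *M leprae* viability. Both measures need a binary call.

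The only step that equalises RNA samples is in the RNA extraction section: "A total of 500 ng of RNA will be converted to cDNA". RLEP DNA is measured in the other portion of the same aspirate, but the article does not relate the RNA signal to it.

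**The concern.** Viability concerns the state of the bacilli that are present. An absolute RNA Ct reflects that state multiplied by the number of bacilli in the sample, and one fixed line cannot tell the two apart. The sampled number may well differ between visits: the needle passes beside one nerve with a saline-prefilled syringe, and the procedure is repeated a year later, after treatment.

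The fixed 500 ng input does not solve this. It sets the mass of total RNA, not the number of bacilli contributing to it. The RNA assay also runs 40 cycles, so a well-formed curve with a Ct between 30 and 40 shows RNA but is recorded as negative.

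At stake is the before-and-after statement on viability. A fall in RNA positivity at 1 year could be taken to show that the remaining bacilli are no longer viable when the data show only that fewer were sampled.

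**Working it through.** **The article's own figures.** It gives no figure for viability. Its one computed figure, 54 per group, concerns diagnostic sensitivity of 70% against 50%. It is reproduced by a one-sample exact binomial test: n = 49, at least 32 positives, upper-tail error 0.0222, power 0.810, and 49 × 1.10 = 53.9, rounded up to 54. It plays no part below.

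**Inputs from the article.** Cut-off Ct 30 (PCR Positivity Criteria); 40 cycles for sodA and 16S; 500 ng RNA; 50 to 100 ng DNA for RLEP (the respective assay sections).

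**Assumptions.** The article gives no PCR efficiency E, no change in load F and no Ct distribution. I take E = 90% to 100% and F = 2 to 100, with RNA per bacillus unchanged.

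**Step 1: shift from load alone.** ΔCt = log(F) / log(1 + E). Every baseline Ct above 30 − ΔCt and up to 30 changes from positive to negative.

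| Fall in load | ΔCt, E = 100% | Baseline Ct that turns negative | ΔCt, E = 90% | Baseline Ct that turns negative |
|---|---|---|---|---|
| 2-fold | 1.00 | 29.0 to 30 | 1.08 | 28.9 to 30 |
| 10-fold | 3.32 | 26.7 to 30 | 3.59 | 26.4 to 30 |
| 100-fold | 6.64 | 23.4 to 30 | 7.17 | 22.8 to 30 |

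For 10-fold at full efficiency: log(10)/log(2) = 3.32, and 30 − 3.32 = 26.68. As a hypothetical case, an RNA Ct of 28 becomes 28 + 3.32 = 31.32. That is negative by the rule but well inside the 40 cycles. The RLEP Ct would rise by the same 3.32 at equal efficiency, so RNA Ct minus RLEP Ct would not move.

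**Step 2: share of baseline positives affected (illustration only).** If baseline RNA Ct were normal with mean μ and SD 3, the share turning negative after a 10-fold fall is 1 − Φ((26.68 − μ)/3) / Φ((30 − μ)/3).

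- μ = 26: 1 − 0.590/0.909 = 35%
- μ = 28: 1 − 0.330/0.748 = 56%
- μ = 30: 1 − 0.134/0.500 = 73%

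The width of this range shows how far the answer depends on a distribution that the article does not give.

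**Step 3: random variation alone.** Suppose the true Ct is 29 at both visits, with an assumed visit SD of 1. Then P(positive) = Φ(1) = 0.841 each time. Positive then negative has probability 0.841 × 0.159 = 0.133; negative then positive has 0.159 × 0.841 = 0.133. The flows are equal and the net change is zero. Only if baseline positives are followed alone does a one-way loss appear, here 0.159.

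**Step 4: what a ratio to RLEP would carry.** DNA input may range from 50 to 100 ng, which by itself moves the RLEP Ct by up to log(100/50)/log(2) = 1 cycle. Under Fine Needle Aspiration, the aspirate is split into two tubes with RNAlater only in the RNA tube, so extraction variation adds to the difference.

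**The case against.** The article never says that RNA-negative means non-viable, and it does not plan to count conversions. It is a condensed report, and a fuller protocol or analysis plan could add normalisation. Its wording on viability is cautious, viability is absent from the numbered specific objectives, and other Ct thresholds are to be explored with receiver operating characteristic curves. A lower load after treatment may also be a real benefit.

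Part of this stands. The non-viable label is an inference from how the article uses RNA, and the load falls and Ct distributions above are assumptions. But the point does not rest on missing detail: the article fixes the Ct 30 rule for RNA samples and offers no other reading of them. The threshold exploration concerns accuracy of the test, and moving the line does not adjust for load. A lower load can be good news without being evidence about the viability of what remains.

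A reader might go further and infer that random variation alone would show up as a treatment effect. The article does not support that. With an unchanged true Ct and equal error at both visits, crossings balance in the two directions (Step 3). A spurious loss needs an analysis restricted to baseline RNA-positives, which is nowhere planned.

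**Conclusion.** The point holds for bacterial load. As written, the RNA rule can turn positive into negative at 1 year with no change in the viability of the remaining bacilli. A 10-fold smaller sampled load does so for every baseline Ct from about 26.7 to 30 at 100% efficiency, or from about 26.4 at 90%. The size of the load change and the share of patients in that band are unknown from the article; the 35% to 73% in Step 2 is illustrative.

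The consequence is limited to the viability statement, which is secondary. The primary accuracy result at Ct 30 and the 54 patients per group are unaffected.

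**What to change.** Keep Ct of 30 or less as the diagnostic positivity rule. For viability, add a separate reading rule:

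1. Draw viability conclusions only from samples whose RLEP DNA is positive. Label RLEP-negative samples not assessable, rather than non-viable.
2. Report RLEP-positive samples with a valid RNA curve at Ct above 30 as their own category, not as evidence that no viable bacilli remain.
3. As a supporting paired analysis, report RNA Ct relative to RLEP Ct from the same aspirate at both visits. Account for the actual DNA input within 50 to 100 ng, and treat RNA non-amplification as censored at the last cycle (40).
4. If changes in RNA positivity are tabulated, show both directions over all paired patients, not only losses among baseline positives.

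The planned assays already produce the Ct values, so no new sampling is needed; the actual DNA input must be recorded for each reaction. The cost is that fewer patients receive a definite viability label at 1 year, and the RNA-to-DNA difference carries extra variation from separate extractions. For that reason it should support the categorical report and not replace it.

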### Sample Calculation

The sample size calculation was based on the prevalence of leprosy, measured at 50% in the target population (patients with suspected leprosy referred to the UHB). Internal data also show that the sensitivity of sputum smear microscopy (standard test for detecting the bacillus) is 50%. A 20% sensitivity gain was arbitrated with perineural aspirate, resulting in a sensitivity of 70% with the proposed technique. Considering a *P* value of less than .05 and a power of more than 0.80 plus a sample increase of 10% to reduce the impact of losses, we arrived at a sample of 54 patients per group (leprosy and nonleprosy) for a total of 108 patients in the study.

The ability of ultrasonography with perineural aspirate to identify patients with leprosy diagnosed via sputum smear microscopy and skin biopsy was analyzed using the area under the curve (AUC). The range of values for the AUC varies between 0.1 and 1. The interpretations for the values are as follows: 0.5 to 0.7 is considered low, 0.7 to 0.9 is considered intermediate, and above 0.9 is considered high [34].

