**Objective:**

This study aims to evaluate the accuracy of ultrasound-guided perineural aspirate in the diagnosis of leprosy. The World Health Organization leprosy composite reference standard will be used as the benchmark for diagnostic accuracy. We will also perform the clinical, molecular, and ultrasonographic follow-up of patients. The study will be performed at the University Hospital of Brasília, a reference center for the treatment of leprosy in the central-west region of Brazil.

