## Methods

### Study Design and Population Studied

This is a diagnostic study with prospective collection. Patients aged 14 years or older will be enrolled after agreeing to and signing the informed consent form. The informed consent form will be signed by the responsible adult in the case of participants under 18 years of age. This research is in line with the Declaration of Helsinki and its revision made in 2013.

The case definition will be determined by a professional external to the investigation according to the standard procedures of the leprosy outpatient clinic of the UHB, which consist of clinical history, general physical examination, and dermato-neurological examination. Case definition will follow the World Health Organization (WHO) composite reference standard for the diagnosis of leprosy [32]. Direct investigation of the bacillus will be performed via SSSs of lesions, earlobes, and elbows. After the procedure, collected material from perineural aspiration and dermal lesions will be sent to the laboratory within a maximum period of 24 hours. The results of the perineural aspiration will only be known to researchers by the end of the study. Morphological data described in the ultrasound examination will be accessed by a blinded ultrasound specialist based on deidentified ultrasound images.

Clinical and molecular examinations will be performed, and their results will be compared to the sonographic findings, which will be collected monthly for 1 year. Molecular findings will be compared to the composite reference standard. Patients will be evaluated clinically, via ultrasound, and molecularly immediately after clinical diagnosis and 1 year after the start of treatment.

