### Case Definition: Composite Reference Standard

All patients with suspected leprosy referred to the outpatient clinic of the UHB will be included. Included patients will be subject to a standardized clinical evaluation and complementary evaluations. Allocation to the leprosy group will be conducted according to the WHO criteria [32], with allocation to the nonleprosy group being reserved for those patients referred by the primary care physician due to suspected leprosy who do not fulfill the WHO’s criteria [32]. Neither ultrasound nor molecular examinations performed on the perineural aspirate will be used in the allocation process. Collection of clinical data and ultrasound examinations with perineural aspirate will be performed on the same day. The diagnostic evaluation will be performed before the index test; as a result, the diagnostic classification provided by the index text will not be known by those responsible for accessing the composite reference standard. Inclusion will occur only after all standard diagnostic tests are conducted.

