Conventional diagnostic tests	Slit skin smear results, bacillary index, and histopathological findings from skin or nerve biopsy (when performed)
Index test—PCR^b^ from perineural aspirate	PCR detection of Mycobacterium leprae targets: RLEP, sodA, and 16S rRNA^c^
Complementary diagnostic test—ultrasound examination	Nerves evaluated: median nerve (carpal tunnel and pronator quadratus), ulnar nerve (ulnar tunnel, immediately before the ulnar tunnel, Guyon canal, and immediately before the Guyon canal), common fibular nerve (fibular head), and tibial nerve (tarsal tunnel and 4 cm above the tarsal tunnel); CSA^d^ measurements; asymmetry indexes (change in CSA^e^ and CSA ratio); focality indexes (change in TPT^f^ and TPT ratio); intraneural or epineural Doppler signal (hypervascularity); nerve echogenicity (normal or abnormal); loss of fascicular pattern; and focal nerve thickening
Reference standard (composite clinical diagnosis)	Presence of ≥1 cardinal sign of leprosy: (1) definite sensory loss in a hypopigmented or reddish skin lesion, (2) thickened or enlarged peripheral nerve with sensory loss and/or muscle weakness, and (3) acid-fast bacilli in slit skin smear

^a^WHO: World Health Organization.

^b^PCR: polymerase chain reaction. PCR targets: RLEP, sodA, and 16S ribosomal RNA of *M leprae*.

^c^rRNA: ribosomal RNA.

^d^CSA: cross-sectional area of the nerve.

^e^Absolute difference between contralateral nerves.

^f^TPT: difference between the thickest and thinnest points along the nerve.

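### The Sample Calculation section ties the AUC to leprosy diagnosed by sputum smear and skin biopsy, which conflicts with the WHO composite reference standard fixed everywhere else in the protocol

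*Protocol article*

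**What the plan says.** The protocol article fixes one reference standard in four places:

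- The Objective in the abstract: "The World Health Organization leprosy composite reference standard will be used as the benchmark for diagnostic accuracy".
- Study Design and Population Studied: "Molecular findings will be compared to the composite reference standard".
- Case Definition: "Allocation to the leprosy group will be conducted according to the WHO criteria". Patients who do not meet those criteria form the nonleprosy group.
- Table 1 (Clinical Data) gives the content, beginning "Presence of ≥1 cardinal sign of leprosy: (1) definite sensory loss in a hypopigmented or reddish skin lesion". The second sign is an enlarged nerve with sensory loss or weakness. The third is acid-fast bacilli in a slit skin smear. One sign is enough.

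The second paragraph of Sample Calculation describes a different target for ultrasonography with perineural aspirate: "identify patients with leprosy diagnosed via sputum smear microscopy and skin biopsy was analyzed using the area under the curve (AUC". This is the only sentence in the article that attaches a reference directly to an AUC. PCR Positivity Criteria plans ROC curves over Ct values, and Diagnostic Accuracy plans AUCs for the quantitative ultrasound variables; neither names a reference.

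Table 1 lists the conventional tests as "Slit skin smear results, bacillary index, and histopathological findings from skin or nerve biopsy (when performed"), separately from the reference standard. The same Sample Calculation paragraph gives the AUC a range of 0.1 to 1.

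**The concern.** The reference standard defines what a diagnostic accuracy study estimates. Two incompatible references leave room to choose between them once results are known.

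The smear-and-biopsy reference also cannot be applied as written. No section plans sputum collection; the smear described everywhere else is a slit skin smear. Biopsy is not one of the three cardinal signs and will be missing for an unspecified share of patients. The sentence does not say whether either test suffices or both are needed.

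The protocol itself says these tests miss many cases. The Rationale puts the sensitivity of smear microscopy or biopsy below 50%. The Discussion says slit skin smear is negative in about 70% of cases and is weakest in early-stage, paucibacillary and pure neural leprosy, the presentations in which the aspirate is expected to help. An AUC against such a reference answers a different question from the sensitivity and specificity reported against the composite, and could not be compared with them.

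**Working it through.** **Inputs from the protocol (Sample Calculation).** 54 leprosy and 54 nonleprosy patients; smear sensitivity 50%; expected aspirate sensitivity 70%. The 54 per group is close to a one-sample test of 70% against 50% (two-sided 0.05, power 0.80): ((1.96×√0.25 + 0.8416×√0.21)/0.2)² = 46.6, so 47, and 52 (47×1.1) or 53 (47/0.9) after the 10% allowance. The point does not turn on this figure; it only supplies the group sizes.

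**Assumptions, not in the protocol.** True index specificity of 95%; smear/biopsy sensitivity equal to the 50% stated for smear; no nonleprosy patient positive on smear/biopsy; and three patterns of overlap between that reference and the index test.

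**Step 1: composite as reference.** Single-threshold AUC = (sensitivity + specificity)/2 = (0.70 + 0.95)/2 = 0.825.

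**Step 2: smear/biopsy as reference, all others counted negative.** Reference-positive = 0.50×54 = 27. Reference-negative = 54 + 27 = 81. Index-positive cases = 0.70×54 = 37.8. False positives among nonleprosy patients = 0.05×54 = 2.7. Let *a* be the number of cases positive on both tests. Then:

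- apparent sensitivity = *a*/27
- apparent false positives = (37.8 − *a*) + 2.7
- apparent specificity = 1 − false positives/81

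| Overlap | *a* | Cases turned false positive | All false positives | Sensitivity | Specificity | AUC |
|---|---|---|---|---|---|---|
| Nested (every reference-positive is PCR-positive) | 27 | 10.8 | 13.5 | 100% | 83.3% | 0.917 |
| 5% of cases smear-positive and PCR-negative | 24.3 | 13.5 | 16.2 | 90% | 80.0% | 0.850 |
| Independent | 18.9 | 18.9 | 21.6 | 70% | 73.3% | 0.717 |

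**Step 3: the 30% smear sensitivity implied by the Discussion, biopsy adding nothing.** Reference-positive = 16.2; reference-negative = 91.8, of whom 37.8 are true cases.

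- Nested: false positives 21.6 + 2.7 = 24.3; specificity 1 − 24.3/91.8 = 73.5%; AUC (1.00 + 0.735)/2 = 0.868.
- Independent: false positives 26.5 + 2.7 = 29.2; specificity 68.2%; AUC (0.70 + 0.682)/2 = 0.691.

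**Step 4: the other reading.** If smear/biopsy selects only the positives, and the negatives remain the WHO nonleprosy group, specificity stays at 95%. With the 50% reference, the AUC is (1.00 + 0.95)/2 = 0.975, (0.90 + 0.95)/2 = 0.925 or (0.70 + 0.95)/2 = 0.825 for the three overlap patterns.

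**The case against.** The strongest reply is that this is stray wording. The sentence sits in the sample-size section, is in the past tense, and names sputum where the other sections name slit skin smear. Four explicit statements elsewhere fix the composite. The main finding is declared to be accuracy at a Ct of 30 or less, and molecular findings are to be compared with the composite. All of this stands, and it limits the point to the AUC analysis. It does not remove the conflict, because this sentence is the only one that gives an AUC its reference.

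The reclassification is also an inference. The sentence says who is to be identified, not who the negatives are. If the negatives are the WHO nonleprosy group, no case is misfiled and the fault is a selected case group (step 4). If either test suffices, smear-negative but biopsy-positive patients stay positive, so 37.8 of 54 misfiled cases at 30% smear sensitivity is a ceiling.

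A reader might infer that the wording turns the target smear-negative cases into false positives and so penalises the test. The documents do not support that. Only index-positive cases can become false positives (10.8 to 18.9 of 27 in step 2); the rest become true negatives. Apparent sensitivity can rise at the same time, and the AUC goes up in two of the three step 2 patterns.

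**Conclusion.** The contradiction is real and is in the current text. As written, the AUC reference conflicts with the WHO composite, names a specimen the protocol does not collect, and relies on a biopsy that only some patients have.

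If reference-negative means everyone not confirmed by smear/biopsy, apparent specificity falls from 95% to about 83%, 80% or 73%, and the single-threshold AUC moves from 0.825 to about 0.92, 0.85 or 0.72. The bias can go either way, so it cannot be allowed for at interpretation. These figures rest on the assumed 95% specificity, a 50% sensitive reference and the assumed overlap patterns. They are single-threshold values, and a full ROC curve over Ct values would differ.

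It would be wrong to conclude that the study's main result is compromised: accuracy at a Ct of 30 or less remains tied to the composite. The point should be fixed, but it does not threaten the primary analysis. The 0.1 to 1 range is a clerical slip; the interpretation bands start at 0.5, so nothing depends on it.

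**What to change.** - State in Diagnostic Accuracy that every ROC and AUC analysis for the diagnosis of leprosy, for PCR Ct values and for ultrasound variables, uses the WHO composite of the Case Definition section as the reference, in line with the main accuracy analysis.
- In Sample Calculation, delete sputum smear microscopy and skin biopsy as the AUC reference. Replace sputum by slit skin smear where the smear sensitivity is given, after confirming that the internal data refer to that test.
- Keep smear and biopsy as comparator tests, as PCR Positivity Criteria already plans, with biopsy compared among those biopsied.
- Leave the viability analyses outside this statement, because the cardinal signs do not define viability.
- Correct the AUC range to 0 to 1, with 0.5 meaning no discrimination.

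The cost is wording only: no change to sample size, data collection or procedures. Aspirate results are withheld until the end of the study and analysis is scheduled from February 2027, so the correction can be fixed before those results are known.
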